#### Exclusion criteria

At the time of recruitment, individuals who have any of the following are not eligible to participate in the study: (i) developed type 2 diabetes mellitus; (ii) are currently pregnant; (iii) have inadequate English language ability to understand the content of the intervention programme; or (iv) have significant cognitive impairment or mental illness.

### Randomisation process

The randomisation process in this RCT will use random permuted blocks to ensure similar numbers of participants in each intervention arm throughout the trial and equal numbers in each arm by the end of the study. In advance of participant recruitment, an independent researcher is responsible for generating the allocation sequence using the free computer software program, Random Allocation Software (version 1.0.0), M. Saghaei, Isfahan University of Medical Sciences, Isfahan, Iran. The same independent researcher is responsible for assigning participants to the intervention groups. Thus, the allocation sequence is concealed from all study researchers until the interventions are assigned.

### Description of interventions/comparison groups

The study is a two-group, parallel randomised controlled trial. As such, following the baseline assessments, eligible participants are randomly assigned to the intervention and control groups in an equal ratio of 1:1. Those assigned to the intervention group receive the 12-week intensive lifestyle programme, Croí MyAction. The programme includes an initial individualised assessment by the multidisciplinary health care team, followed by 12 sessions of 2.5 hours each per week (delivered in a maximum of 16 weeks^b^). Each of the weekly sessions comprises a one-hour group exercise programme, a group health promotion and education seminar, and one-to-one meetings to review individual health goals with a specialist nurse, physiotherapist and dietician. As previously mentioned, each Croí MyAction participant is invited to enroll a family member, spouse, friend or other partner in the programme with them for support and motivation outside the programme hours. The intervention is conducted in groups of similar sizes on the same site with the same facilitators, thus ensuring standardised delivery.

The control group receives the standard health care advice provided to women with prior GDM. In this study, standard care is defined as: (i) the provision of educational pamphlets for reducing diabetes risks - particularly, healthy eating and regular physical activity; and (ii) care prescribed by a woman’s general practitioner (GP) as required. It is recognised that GP care will vary from individual to individual.

### Outcomes

The primary outcome measure in the study is glucose dysfunction, which will be assessed in terms of a mean reduction in fasting plasma glucose levels from the time of the baseline assessment to the one-year follow-up assessment, on a 75 gram oral glucose tolerance test. Seven secondary outcomes will also be measured at the baseline and one-year follow-up assessments; namely: two-hour postprandial (PP) blood glucose levels on a 75 gram OGTT, insulin resistance, diet adherence, weight and shape, physical activity and fitness, lipid profile, and psychological evaluation. For participants in the Croí MyAction arm of the study, a number of these outcomes will also be measured immediately following the intervention. Table 1 outlines the definitions, measurement techniques and time points for each of the secondary outcomes.

### Analysis plan

#### Quantitative analysis

All participants will be invited back for one-year follow-up tests to evaluate the effects of the Croí MyAction programme on the same biomedical, anthropometric and psychological measures administered at the baseline assessment. These quantitative data will be analysed in a variety of ways, focusing on comparisons within individual participants (that is, before and after the intervention) and between the study arms (that is, comparing the cohort of women who received the Croí MyAction intervention to the control group participants). In the first instance, a number of numerical and graphical summaries will be used to summarise the groups at baseline and the within-participant correlation structure, pre- and post-intervention. A linear mixed model will be used to compare the change in mean FPG values across time, adjusting for variables, such as age and parity, as relevant. Basic statistical analyses will also be performed to compare data collected from participants in the intervention arm at the end of the Croí MyAction programme and at the one-year follow-up appointment to assess the sustainability of any health improvements made through participation in the intervention.

In the case of missing data, an intention-to-treat analysis will be performed using multiple imputations (based on 10 imputations) and a predictive model-based method. In this method, each missing value is replaced by 10 imputed values, which are generated via random draws from the Bayesian posterior distributions arising from regression models based on chained equations. The selection of explanatory variables for inclusion in the final model will be based on a combination of clustering, tree-based methods and variable selection techniques applied to the complete cases and to the imputed data.

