### Sample size and power calculation

The sample size required for the RCT is 54 participants. This number was calculated based on estimates provided from pilot data from a group of women with a history of GDM (n = 74) receiving conventional health care. The pilot group had a standard deviation of 0.64 mmol/l for the difference in fasting plasma glucose (FPG) on an oral glucose tolerance test between two time points: approximately three months post-pregnancy and then one to three years later. Given the standard deviation, it is estimated that a sample size of 27 in each study arm is necessary to have 80% power to detect a mean difference of 0.5 mmol/l in FPG between baseline and one-year follow-up in the two study arms, using a two-sample t-test at the 0.05 significance level.

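### The primary FPG comparison is framed as change, and conditioning on baseline FPG is not prespecified but left to an open covariate list and data-driven selection

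*Protocol article*

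**What the plan says.** The protocol article treats the primary comparison as one of change in three places.

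- **Outcomes:** the primary measure is the "mean reduction in fasting plasma glucose levels from the time of the baseline assessment to the one-year follow-up assessment".
- **Sample size and power calculation:** the trial is sized to "detect a mean difference of 0.5 mmol/l in FPG between baseline and one-year follow-up in the two study arms". The method behind that number is given as "using a two-sample t-test at the 0.05 significance level". The SD of 0.64 mmol/l is that of the within-woman difference in a pilot group of 74 women under conventional care.
- **Quantitative analysis:** "A linear mixed model will be used to compare the change in mean FPG values across time". Covariates are mentioned only by way of example: "adjusting for variables, such as age and parity, as relevant". The same section says that the explanatory variables in the final model will come from clustering, tree-based methods and variable selection, applied to the complete cases and to the imputed data.

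Baseline FPG is not named as a covariate, and nothing says that the arms share a baseline mean in the mixed model. Nothing rules out either one.

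**The concern.** Baseline FPG is the baseline value of the primary outcome, is measured before randomisation, and would usually be among the strongest predictors of FPG at one year. Age and parity are named and baseline FPG is not. Calling the analysis a linear mixed model does not settle the matter. If both visits are responses and each arm has its own baseline mean, the arm-by-time term is the change-score contrast when data are complete.

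The stake is precision. The change score subtracts the whole of the baseline value, whereas a baseline-conditioned analysis subtracts only the part that predicts follow-up. A chance difference in baseline FPG between two arms of 27 therefore passes in part into the change estimate. If baseline FPG enters only when a selection procedure picks it, the form of the primary estimate also depends on the outcome data.

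**Working it through.** **Inputs from the protocol article:** SD of change 0.64 mmol/l, difference 0.5 mmol/l, 27 per arm, 1:1 allocation, alpha 0.05, two-sample t-test (all from the sample size section, except the allocation ratio, which is under the description of interventions). **Assumed, not given:** the correlation r between baseline and one-year FPG, taken as 0.3 to 0.8, and equal FPG variance at the two visits. The last step relaxes the equal-variance assumption.

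**1. The plan's own figure.** The standardised difference is 0.5/0.64 = 0.781. A two-sided t-test at 0.05 with 80% power needs 26.7, hence 27 per arm, and power at 27 is 80.4%. The normal approximation gives 26 per arm. A one-sided t-test would need only 21. The stated 27 is therefore reproduced as a two-sided t-test on change.

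**2. What the model estimates.** With two visits, complete data and a separate mean for each arm at each visit, the arm-by-time coefficient is (one-year mean − baseline mean) in the intervention arm minus the same quantity in the control arm. This is the change-score difference, so the t-test calculation describes its power.

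**3. Conditioning on baseline, equal variances.** Let σ be the SD of FPG at either visit.

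- Variance of change: 2σ²(1 − r)
- Residual variance given baseline: σ²(1 − r²)
- Ratio: (1 + r)/2
- Residual SD: 0.64 × √((1 + r)/2)

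Power below uses the noncentral t with 2 × 27 − 3 = 51 degrees of freedom.

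| r | Variance ratio | Residual SD | Power at 27 per arm | n per arm for 80% |
|---|---|---|---|---|
| 0.3 | 0.65 | 0.516 | 93.7% | 18 |
| 0.5 | 0.75 | 0.554 | 90.2% | 21 |
| 0.7 | 0.85 | 0.590 | 86.3% | 23 |
| 0.8 | 0.90 | 0.607 | 84.3% | 25 |

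The change analysis stays at 80.4% in every row.

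**4. Simulation check**, 10,000 trials at each r:

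| r | Power, change | Power, ANCOVA | Variance ratio | Correlation of change estimate with baseline difference |
|---|---|---|---|---|
| 0.3 | 80.9% | 93.7% | 0.67 | −0.58 |
| 0.5 | 80.5% | 89.3% | 0.76 | −0.50 |
| 0.7 | 80.5% | 85.4% | 0.87 | −0.39 |

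Both estimators average about −0.50, so neither is biased. The ANCOVA estimate is uncorrelated with the baseline difference (within 0.01 of zero). Its variance ratios lie slightly above (1 + r)/2, which is the small-sample price of estimating the slope.

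**5. Effect of a chance imbalance.** Take a baseline difference of one standard error of the difference in arm means, σ√(2/27), with σ = 0.64/√(2(1 − r)). The change estimate shifts by (1 − r) × σ × √(2/27) = 0.64 × √((1 − r)/27). At r = 0.3, 0.5, 0.7 and 0.8 this is 0.103, 0.087, 0.067 and 0.055 mmol/l, or 21% down to 11% of the 0.5 mmol/l target.

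**6. If the variances differ.** With SDs s1 at baseline and s2 at one year, conditioning saves (s1 − r·s2)² out of a change variance of s1² + s2² − 2r·s1·s2. Take s1/s2 = 0.7 as an illustration (neither SD is given) and set s2 = 1:

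- r = 0.3: 0.16/1.07 = 15% saved
- r = 0.5: 0.04/0.79 = 5% saved
- r = 0.7: 0/0.51 = 0% saved

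Under equal variances the savings were 35%, 25% and 15%. At r = 0.7 the shift from imbalance vanishes as well.

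**The case against.** The strongest reply is that the article does not fix an unconditioned model. Age and parity are examples, the list is open, and a mixed model with a common baseline mean would be essentially equivalent to ANCOVA. A journal article also commonly leaves the exact specification to a fuller plan. This stands in part: a reader might infer that the primary model omits or excludes baseline FPG, and the text does not support that. But the article is not merely silent. It says that the final explanatory variables will be chosen by data-driven methods, and that is a poor way to decide whether the baseline of the primary outcome enters a confirmatory comparison.

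Three other strong readings fail.

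- **That the change analysis is biased.** It is unbiased over randomisation. The shift in step 5 applies only given an imbalance actually drawn.
- **That selecting women on raised FPG builds regression to the mean into the treatment effect.** Such regression affects both arms equally in expectation, and raised FPG is only one of three alternative entry routes.
- **That the trial is underpowered for this reason.** Outcome, sample size and analysis agree on change, and 27 per arm gives the planned 80%.

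The reply that the gains rest on unstated assumptions also stands. They need an assumed r and equal variances. Equal variances may not hold, because women who already have diabetes are excluded at entry, which limits the spread of baseline FPG but not of follow-up FPG.

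**Conclusion.** The point holds as an improvement that costs nothing, not as an error. The protocol article does not prespecify conditioning on baseline FPG, and its ordinary reading with two visits is the change-score contrast: valid, with 80.4% power at 27 per arm, but generally less precise than the alternative and exposed to chance imbalance in a trial of 54.

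Under equal variances and r of 0.3 to 0.8, conditioning would raise power by about 13 to 4 percentage points and remove a shift of about 0.10 to 0.055 mmol/l per standard error of baseline imbalance. These figures are illustrations. The gain shrinks as r approaches 1, and it can fall to about nothing if baseline FPG varies less than follow-up FPG. The article specifies no models for the individual secondary outcomes, so the point is confined to the primary analysis.

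**What to change.** Prespecify one of two forms for the primary analysis:

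- ANCOVA of one-year FPG on arm, with baseline FPG as a forced covariate, plus age and parity; or
- a longitudinal model with both visits as responses and the baseline mean constrained to be equal across arms.

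In either form, keep baseline FPG outside the variable-selection step. Listing baseline FPG as a further covariate while it also remains a response with arm-specific means would not achieve the aim, because the arm-by-time term would still be a contrast of changes.

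The effect remains a difference in mmol/l, comparable with the 0.5 used for sizing, and the sample size need not change. Baseline FPG is already measured, so the cost is a sentence of wording, fixed before outcome data are examined.

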#### Qualitative analysis

Following the RCT, qualitative research will be undertaken to explore the perceptions, views and experiences of women who participated in the randomised controlled trial, comparing Croí MyAction participants with those who followed usual care. This work includes an exploration of the barriers and facilitators to maintaining lifestyle changes. Toward this end, semi-structured, one-to-one interviews will be conducted with 20 participants, 10 from the intervention arm and 10 from the control arm, within six months of completion of the Croí MyAction programme. Participants will be purposively selected to ensure that a representative range of characteristics, such as age and diabetes risk factors at the time of recruitment, are taken into account. All interviews will be recorded and transcribed; data analysis will be based on themes derived from the transcripts. NVivo, a qualitative software package developed by QSR International, Melbourne, Austrlia, will be used to facilitate data management and analysis.

#### Economic evaluation

Finally, an economic evaluation, incorporating both cost-effectiveness analysis and cost-utility analysis, will be performed to explore the cost-effectiveness of the Croí MyAction lifestyle modification programme for women with prior GDM. The economic evaluation will be undertaken in a manner consistent with the guidelines issued by the Health and Information Quality Authority in Ireland [25]. Data will be collected throughout the trial on resource use and outcome measures; these will provide the basis for the analysis. Data will be collected via patient questionnaires on: (a) the costs falling on health and social care systems, and (b) the costs falling on individuals and families. Factors that contribute towards health and social care costs include hospital visits, inpatient stays, GP visits, medicines and other treatments. Factors that contribute towards private costs include travel expenses, time input, and child-minding expenses. Unit costs will be used to convert data on resource use to costs of care. Incremental analysis will be used to provide information on the marginal costs and effects of the programme relative to standard care through the calculation of incremental cost-effectiveness ratios. In terms of effectiveness, the cost-effectiveness analysis will incorporate the primary and secondary outcomes considered in the trial. In addition, the cost-utility analysis will consider effectiveness in terms of Quality Adjusted Life Years (QALYs), as estimated from patient responses to the EuroQol EQ-5D measurement tool [26]. Uncertainty in the analysis will be explored using a combination of univariate and multivariate sensitivity analyses and decision uncertainty will be presented using cost-effectiveness acceptability curves.

## Trial status

Enrolment into the study started on 14 June 2012. Recruitment is expected to be complete by March 2013.

## Endnotes

^a^ The glucose levels used to diagnose impaired fasting glucose and impaired glucose tolerance are based on the 2010 recommendations of the American Diabetes Association and the International Association of Diabetes and Pregnancy Study Groups (IADPSG) [27].

^b^ The Croí MyAction programme allows for participants to complete the 12-week curriculum within 16 weeks, thus accommodating for planned or unplanned events prohibiting participation in a weekly session.

## Abbreviations

BMI: Body mass index; DASS-21: 21-item Depression, Anxiety and Stress Scale; DIP: Diabetes in pregnancy; FPG: Fasting plasma glucose; GDM: Gestational diabetes mellitus; GP: General practitioner; HDL: High-density lipoprotein; HOMA: Homeostasis Model Assessment; HRB: Health Research Board; HSE: Health Service Executive; IADPSG: International Association of Diabetes and Pregnancy Study Groups; IFG: Impaired fasting glucose; IGT: Impaired glucose tolerance; IR: Insulin resistance; LDL: Low-density lipoprotein; MetS: Metabolic syndrome; METS: Metabolic equivalents; MHI-5: Mental Health Index 5; NGT: Normal glucose tolerance; OGTT: Oral glucose tolerance test; PET: Pre-eclampsia toxaemia; PIH: Pregnancy induced hypertension; PP: Postprandial; QALY: Quality-adjusted life year; RCT: Randomised controlled trial.
